#### Blood Pressure Measurement

Blood pressure readings will be taken using the Omron 705IT (HEM-759P-EZ) blood pressure machine. A SOP will be made available which will detail procedural instructions. Systolic and diastolic blood pressure will be recorded and interpreted in accordance with NICE guidelines on Hypertension (CG127). The device will be calibrated yearly and yearly calibration certificates will be available. The results are not indicative of the treatment that the patient is receiving and will therefore be recorded by the research fellow.

#### Blood test analysis

All clinical laboratory procedures will be undertaken by:

**Pathology Department, City Hospital, [name].  
[contact]**

Blood tests will be taken after patient written informed consent has been received and electronic requisitions will be completed. Specimens will be labelled as per Trust guidelines, a copy of the requisition will be retained.

Blood test results can be reviewed electronically, a copy will be printed. These will be reviewed and signed on a daily basis by the trials physician listed on the delegation log with this delegated duty

Blood samples will be used for routine laboratory checks done in City Hospital laboratory. With the participants consent, part of the blood samples will also be stored frozen in the study centre in City Hospital for future analysis of markers, which would help to better understand the study findings and mechanisms of the disease. Blood samples will not be used to perform any genetic analysis for this study.

For the screening visit, if blood test results are available from City Hospital Pathology Department which were obtained within 30 days of the screening visit, these test results will be used for

|                          |            |               |            |       |          |
|--------------------------|------------|---------------|------------|-------|----------|
| Trial name:              | IMPRESS-AF |               |            |       |          |
| Protocol version number: | 6.0        | version date: | 12/10/2015 | Page: | 31 of 67 |

---

assessment at screening. If the results are abnormal and there is a clinical reason to repeat the tests or no results are available, blood samples will be taken.

### 8.3 Schedule of Assessments

The schedule of assessments and investigations required is described below.

Screening: As described earlier

#### Baseline (participants who meet the inclusion criteria)

- Eligibility reviewed
- Medical history and medication review
- Standard clinical examination (including BP measurement)
- Cardiopulmonary exercise testing (CPET) with determination of peak VO2
- 6 minute walking test
- EQ-5D and MLWHF quality of life questionnaires will be completed
- Randomisation to spironolactone or placebo
- Prescription and dispensing of blinded medication by qualified medical research personnel

#### Follow-up (months 1, 3, 6, 9, 12, 15, 18 and 21)

- Standard clinical examination (including BP measurement),
- Concomitant medication review
- Blood samples to test renal function, potassium, sodium and full blood count (including hematocrit).
- EQ-5D and MLWHF quality of life questionnaires will be completed at months 12 only.
- Information on outcomes such as hospitalisations and major adverse clinical events (MACE) will be collected, as well as safety outcomes (assessment of symptoms and possible side effects)
- Prescription and dispensing of blinded medication by qualified medical research personnel

#### Final Visit (24 months from randomisation)

- Standard clinical examination (including BP measurement),
  - Medication review
  - Repeat ECG
  - Repeat echocardiogram
  - Repeat Brain Natriuretic Peptide (BNP) level test using point of care device
  - Repeat Cardiopulmonary exercise testing (CPET) with determination of peak VO2
  - Repeat 6-minute walk test
  - Blood sample taken: potassium, sodium, full blood count (including hematocrit) and renal function
  - EQ-5D and MLWHF quality of life questionnaires will be completed
- If the patient has an indication for spironolactone, the participants GP will be informed. No further follow up will be arranged. The GP will be informed about the trial completion.

#### Additional Visits (special conditions)

- Within 1 week of every dose adjustment a blood test will be taken for analysis renal function, potassium and sodium
- The results will be sent to the RC-CCS and reviewed by the trial Research fellow. A fraction of patients may have increase in potassium related to spironolactone. Based on the test results it might be necessary to stop the drug or reduce its dose.
- Participants may voluntarily request withdrawal from treatment. These participants will be requested to return any remaining medication to the RC-CCS. Where patients are only withdrawing from treatment but still wish to take part in the trial, patients will be requested to complete the QoL questionnaires at months 12 and 24.

|                          |            |               |            |       |          |
|--------------------------|------------|---------------|------------|-------|----------|
| Trial name:              | IMPRESS-AF |               |            |       |          |
| Protocol version number: | 6.0        | version date: | 12/10/2015 | Page: | 33 of 67 |

---

## 8.4 Participant Withdrawal

Participants will be withdrawn from the **trial** if written informed consent is revoked by the participant.

Participants will be withdrawn from the **trial medication** in the following cases:

- Potassium level to  $>5.5$  mmol/L.
- Severe renal impairment (e.g. acute renal failure, creatinine  $>220$   $\mu\text{mol/L}$ , creatinine clearance  $<30$  mL/min)
- Significant breast pain or gynaecomastia despite reduction in the trial medication dose (see above)
- Allergy to the trial drug

The participant will be requested to return any remaining medication to the RC-CCS.

Where participants are withdrawing from the trial medication only, but still wish to take part in the trial, they will be asked to complete the QoL questionnaires at months 12 and 24.

---

|                          |            |               |            |       |          |
|--------------------------|------------|---------------|------------|-------|----------|
| Trial name:              | IMPRESS-AF |               |            |       |          |
| Protocol version number: | 6.0        | version date: | 12/10/2015 | Page: | 34 of 67 |

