In the event of a codebreak situation occurring, City Hospital Pharmacy Department will be alerted and will follow the instructions on the codebreak form; all fields must be completed before performing the codebreak. The PC-CRTU should be informed as soon as possible if the code has been broken. This must be done by sending a copy of the completed codebreak form to the PC-CRTU via email or fax. The codebreak envelope must also be resealed as soon as possible; the time and date of the codebreak should be documented, along with the name of the person performing the codebreak, and the reason for the codebreak.

Once the code is broken, the patient will be withdrawn from the trial treatment, as they will become unblinded to their trial drug. However, where applicable, these patients will be asked to complete the QoL questionnaires at the 12 month and 24 month visits. Please refer to the patient withdrawal section for more information.

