### 7.2 Treatment and Dosing Schedule

Trial participants will receive either Spironolactone or matched placebo according to the following instructions:

- a single 25 milligram tablet
- to be taken orally once per day (typically to be taken during the morning, but can be taken regularly at other time of day if preferable).
- to be taken with a drink to help swallowing of the drug
- for a 24 month period

In the case of an increase in potassium level to 5.1-5.5 mmol/L or in the presence of other non-life-threatening side effects (such as gynaecomastia), the trial drug will be down-titrated to 25 mg each second day. In such cases, the investigators are advised to re-up-titrate the trial medication if the reason for down-titration has resolved. Routine laboratory surveillance of serum potassium, sodium, full blood count with hematocrit, and renal function will be done by protocol at each visit and within 1 week of any dose adjustment.

Drug toxicity will be defined as an increase in potassium level to >5.5 mmol/L. In the case of toxicity or suspected toxicity, the trial medication will be stopped for the duration of the trial, but the patient will be requested to attend the remaining follow up visits.

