### 9.4 Reporting period

Details of all AEs will be documented and reported from the date of consent (screening) until 7 days after the last dose.

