## 13. STATISTICAL CONSIDERATIONS

### 13.1 Analysis of Outcome Measures

Analysis will follow intention to treat principles (ITT) Following data cleaning, levels of demographics gathered at primary screening will be quantified using basic statistics (mean, SD, Median, IQR) and graphical presentations (boxplots, histograms, scatter plots) Sub division will be made by intervention /control and stratum. Likewise levels of primary and secondary outcomes at baseline will be similarly reported. Prior to any substantial analysis, preliminary impression of trends in longitudinal measurements will be provided graphically, separately for intervention and control participants.

1. Linear mixed model analysis will be used to compare peak  $VO_2$  at two years between the intervention and the control group Covariates will be baseline peak  $VO_2$ , age, gender systolic/diastolic blood pressure and BMI measured at baseline. GP practices or recruitment centres will be included as random effects to enable findings from this trial to be judged in the context of a different group of GP practices

2. Further exploratory analyses will incorporate interaction terms between intervention/control and each of the covariates. Backward elimination will be used to remove non significant interactions and then non significant main effects. If residuals from mixed model analysis violate the assumption of a normal distribution as tested by Kolmogorov Smirnov test then transformation of the dependent variable or bootstrap analysis will be conducted. Transformations considered will be those in the Box Cox family i.e. power and log. Bootstrap analysis will involve sampling with replacement 1000 sets of data from the original data, each of the same size as the original dataset Each set will then be analysed in the same manner as the original dataset This will enable an empirical distribution of each test statistic to be formed and relocated at its null hypothesis value Significance of the statistics in the original data will then be determined from the appropriate tail area of the empirical null distribution.

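### Sections 6.3, 8.3 and 8.4 ask participants who stop trial medication only for QoL questionnaires, section 7.2 asks an overlapping group for all visits, and no rule clearly secures the month-24 peak VO2 off drug

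*Protocol*

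**What the plan says.** Section 8.4 separates leaving the trial (consent revoked) from leaving the trial medication. Its reasons for the second are potassium above 5.5 mmol/L, severe renal impairment, breast symptoms that persist after dose reduction, and allergy. For people in this group it says "but still wish to take part in the trial, they will be asked to complete the QoL questionnaires at months 12 and 24".

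Two other sections match it. Section 8.3, under Additional Visits, says of people who choose to stop treatment but stay in the trial that "patients will be requested to complete the QoL questionnaires at months 12 and 24". Section 6.3 says that after a codebreak "these patients will be asked to complete the QoL questionnaires at the 12 month and 24 month visits", and sends the reader to the withdrawal section.

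Section 7.2 differs. It states "Drug toxicity will be defined as an increase in potassium level to >5.5 mmol/L". After toxicity or suspected toxicity the medication is stopped for the rest of the trial, "but the patient will be requested to attend the remaining follow up visits".

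The final-visit list in section 8.3 includes "Repeat Cardiopulmonary exercise testing (CPET) with determination of peak VO 2", with ECG, echocardiogram, 6-minute walk test and QoL. The assessment table in section 8 places CPET at baseline and month 24 only. Section 13.1 states "Analysis will follow intention to treat principles (ITT" and specifies multiple imputation for missing values. On safety data, section 9.4 says "Details of all AEs will be documented and reported from the date of consent (screening) until 7 days after the last dose".

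**The concern.** The primary outcome needs a clinic test at month 24. A site that applies 8.4 as written would ask a participant who has stopped medication for two sets of questionnaires and could reasonably think it had done all that was required. Section 10.2 even allows questionnaires to be completed at home and posted when they cannot be done in clinic, so a request for QoL does not by itself bring the participant to the visit where CPET is done.

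The participants concerned are unlikely to be a random subset. Section 8.3 expects potassium rises related to spironolactone, and section 9.3.1 lists side effects requiring withdrawal of treatment among the expected events. Missing peak VO2 could therefore be more frequent in the active arm and linked to how those participants fared. No intermediate CPET exists to inform the imputation. An analysis plan cannot recover tests that were never requested, so the matter belongs in the protocol's follow-up instructions.

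**Working it through.** **1. The follow-up instructions side by side**

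| Reason for stopping medication | Section | Follow-up requested |
|---|---|---|
| Potassium above 5.5 mmol/L | 7.2 | All remaining visits |
| Potassium above 5.5 mmol/L | 8.4 | QoL at months 12 and 24 |
| Renal impairment, breast symptoms, allergy | 8.4 | QoL at months 12 and 24 |
| Participant's choice | 8.3 | QoL at months 12 and 24 |
| Codebreak | 6.3 | QoL at the month 12 and 24 visits |

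The first two rows give the same participant two instructions. For the remaining rows no section clearly keeps the clinic visits, unless the case is classed as suspected toxicity under 7.2.

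**2. The protocol's own sample size**

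Inputs from section 13.1.1: difference 2 ml/min/kg, SD 5, two-sided 5% t-test, 100 per group, 20% loss, 250 in total. With n per group, the noncentrality is 2 / (5 × √(2/n)) on 2n − 2 degrees of freedom.

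- n = 100: noncentrality 2.83, power 80.4%. The stated 80% is reproduced.
- 200 / 0.8 = 250. The stated total is reproduced.
- n = 125 (no loss): power 88.3%. The stated 88% is reproduced.

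**3. If stopping medication adds to the missing CPETs**

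The protocol gives no stopping rate, so x below is an assumption: the share of randomised participants, beyond the planned 20%, who have no month-24 CPET. Evaluable n per group = 125 × (0.80 − x). Total needed to keep 200 evaluable = 200 / (0.80 − x).

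| x | n per group | Power for 2 ml/min/kg | Total needed |
|---|---|---|---|
| 0 | 100 | 80.4% | 250 |
| 5% | 93.75 | 77.8% | 267 |
| 10% | 87.5 | 74.9% | 286 |
| 15% | 81.25 | 71.7% | 308 |
| 20% | 75 | 68.2% | 334 |

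Section 13.1.1 describes the 20% as 5% per year from death and 5% per year from other reasons, which it does not define. If those reasons already include people who stop medication, x = 0 and power is unchanged.

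**4. Illustration of bias**

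Suppose a fraction f of the active arm stops, loses the whole 2 ml/min/kg benefit, has no CPET, and is imputed as if still treated. The ITT effect is 2 × (1 − f) but the estimate is 2, so the overstatement is 2f: 0.2 ml/min/kg at f = 10% and 0.4 at f = 20%. All four conditions are assumptions.

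**5. Hospitalisations**

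Section 8.3 collects these as an outcome at the follow-up visits at months 1 to 21, separately from adverse event forms, and section 2.2 sets the period as the 2-year follow-up. They are at risk only if the visits lapse. Adverse event reporting, which closes 7 days after the last dose, would then not fill the gap.

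**The case against.** The best defence is that the QoL sentences add to the schedule and do not replace it. Section 8.4 treats someone who stops medication as still in the trial. Section 3.1 times the final visit from randomisation, not from the last dose, and says that it assesses the primary and secondary outcomes. The final-visit list carries no on-drug condition, and section 6.3 mentions the month 12 and 24 visits as if they will take place. No section says that CPET or the other tests are dropped.

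This stands in part. It rules out three stronger conclusions that a reader might draw:

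- That the 2-year peak VO2 is lost in everyone who stops. The tests are unmentioned in 6.3, 8.3 (on voluntary withdrawal) and 8.4, not excluded, and section 7.2 keeps the visits for toxicity stops.
- That an ITT analysis cannot be done. Section 13.1 specifies analysis on ITT principles with multiple imputation. That can be run; the issue is how much it must lean on untestable assumptions. The imputation model may also be detailed in an analysis plan that is not shown.
- That hospitalisations after stopping are lost. They have their own collection route at visits.

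The defence does not remove the contradiction between 7.2 and 8.4 for potassium. Nor does it explain why three sections single out QoL if the whole schedule is meant to continue. Section 7.2 shows that the authors wrote a request for all visits where they intended one.

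**Conclusion.** The point holds as an inconsistency with consequences for the primary outcome. For potassium stops the protocol contradicts itself. For other stops it does not clearly secure the month-24 CPET, 6-minute walk test, echocardiogram and ECG. Under the literal reading of 8.4, the ITT comparison of peak VO2 depends on imputation for participants whose missingness is plausibly related to treatment.

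The size cannot be established from the protocol. A power of about 75% to 68% applies only if a further 10% to 20% of randomised participants, beyond the 20% allowance, have no CPET. If the allowance already covers them, power stays at 80% and only the risk of bias remains. The 0.2 to 0.4 ml/min/kg overstatement is an illustration and not an estimate.

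**What to change.** Reconcile sections 6.3, 8.3 and 8.4 with 7.2 in one follow-up rule, cross-referenced from each:

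- Every randomised participant who has not withdrawn consent is asked to attend the remaining visits, on or off drug. Month 24 includes the full outcome set (CPET, 6-minute walk test, echocardiogram, ECG, QoL) where the participant is able to perform it.
- Deaths and all-cause admissions are recorded to 24 months in everyone, whatever the date of the last dose.
- Section 13.1 states that observed off-drug values are used in the ITT analysis.

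The rules for stopping or adjusting medication are not affected. The cost is a protocol amendment and some additional follow-up visits for participants off drug, using visits and tests already in the schedule. The protocol gives no budget from which to price them.

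The change protects validity more than power. If 10% or 20% of the active arm stopped and lost all benefit, the ITT effect would be 1.8 or 1.6 ml/min/kg, and power at 100 per group would be 71.7% or 61.5%. That would reflect the treatment policy being tested and is no reason to leave the values uncollected.

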## 9. ADVERSE EVENT REPORTING

### 9.1 Reporting Requirements

The collection and reporting of Adverse Events (AEs) will be in accordance with the Medicines for Human Use Clinical Trials Regulations 2004 and its subsequent amendments. The CI or PI will assess the seriousness and causality of all AEs experienced by the participant, and the CI will assess the expectedness of all SARs. This will be documented in the source data with reference to the safety information contained within the Summary of Medicinal Product Characteristics (SmPC).

Spironolactone has a half-life of about 1–2 hours, but it has active metabolites with longer half-lives. Therefore the end point for the reporting of serious adverse event will be 7 days after the last dose.

### 9.2 Adverse Events (AE)

All medical occurrences which meet the definition of an AE should be recorded on the AE pages of the CRF. Please note this includes abnormal laboratory findings. All AEs recorded on the AE CRF must be followed up to resolution and patients must be asked if they have experienced any AEs at every visit.

### 9.3 Serious Adverse Events (SAE)

Investigators will report all AEs that meet the definition of serious to the PC-CRTU. A SAE Form should be completed for each event and must be faxed to the PC-CRTU trials team immediately.

#### 9.3.1 Events that do not require reporting on a Serious Adverse Event Form

The following are regarded as expected events for the purpose of the trial and should not be reported on an SAE form. These events should be collected on the routine CRFs instead.

- (i) development of hyperkalaemia ( $>5.0$  mmol/L)
- (ii) a rise in creatinine to  $>220$   $\mu\text{mol/L}$
- (iii) development of gynecomastia
- (iv) development of side effects requiring withdrawal of the trial treatment

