### 6.3 BLINDING

Trial participants, the trial team in contact with the patient, care providers, outcome assessors and data analysts will all remain blinded to the treatment after assignment to interventions.

Blinding of the trial drug identity will take place at the time of packaging and labelling. The trial drug will be overencapsulated and packaged by Catalent Pharma Solutions, who will be supplied with the IMP Number List by the PC-CRTU computer programmer. The IMP Number List will also state which of A or B represents the spironolactone, and which the placebo, and Catalent Pharma Solutions will use this information to label the medication bottles accordingly. Overencapsulation and bottle labelling will be performed in one run for spironolactone and a completely separate run for placebo. Medication bottles will be labelled only with the unique IMP number, and the label will not indicate whether the contents are active or placebo. Catalent Pharma Solutions will also produce six spare bottles of trial medication (three each of spironolactone and placebo, randomly assigned by the computer programmer to IMP Numbers 251P-256P). In the event of a patient losing their medication, the computer will allocate to that patient another number corresponding to a spare medication bottle for the same trial arm.

Only the computer programmer and Catalent Pharma solutions will see the IMP Number List (and thus be unblinded to the trial arms), however 256 individually numbered security-sealed envelopes, each containing the respective codebreak, will also be supplied to the Pharmacy Department at City Hospital (who are independent of the trial, and operate 24 hours a day). City Hospital Pharmacy Department will be responsible for unblinding in the event of an emergency codebreak situation occurring. Codebreaks of the trial drug will be restricted to emergency situations only; these will be rare, as any sick patient will be treated symptomatically, and their management will not usually be altered by knowing the identity of the trial compound (i.e. spironolactone or placebo). Unblinding should be avoided unless knowledge of the trial treatment is essential for the correct clinical care of the patient, e.g. in the cases of acute liver injury, acute renal failure, Stevens-Johnson syndrome or agranulocytosis, if suspected to have been caused by spironolactone. Cases that are considered serious, unexpected and possibly, probably or definitely related will be unblinded.

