## 9.9 Data Monitoring and Ethics Committee

Data analyses will be supplied in confidence to an independent Data Monitoring and Ethics Committee (DMEC), which will be asked to give advice on whether the accumulated data from the trial, together with the results from other relevant research, justifies the continuing recruitment of further participants. The DMC will operate in accordance with a trial specific charter based upon the template created by the Damocles Group. The DMC will meet every 6 months unless there is a specific reason (e.g. safety phase) to amend the schedule. The DMEC will review all SAEs.

|                          |            |               |            |       |          |
|--------------------------|------------|---------------|------------|-------|----------|
| Trial name:              | IMPRESS-AF |               |            |       |          |
| Protocol version number: | 6.0        | version date: | 12/10/2015 | Page: | 37 of 67 |

Additional meetings may be called if recruitment is much faster than anticipated and the DMC may, at their discretion, request to meet more frequently or continue to meet following completion of recruitment. An emergency meeting may also be convened if a safety issue is identified. The DMC will report directly to the Trial Steering Committee who will convey the findings of the DMC to the sponsor. The DMEC may consider recommending the discontinuation of the trial if the recruitment rate or data quality are unacceptable or if any issues are identified which may compromise participant safety. The trial would also stop early if the interim analyses showed differences between treatments that were deemed to be convincing to the clinical community.

The trial may be stopped due to poor recruitment.

The DMEC will be responsible for the regular monitoring of trial data. The DMEC will assess the progress of the trial and give advice on whether the accumulated data from the trial, together with the results from other relevant trials, justifies the continuing recruitment of further participants. The committee will meet in person or by teleconference prior to the trial commencing and then three and six months after initiation of the trial. The DMC will make confidential recommendations to the TSC as the decision –making committee for the trial.

Currently agreed DMEC members

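### Section 9.3.1 keeps four kinds of event off the SAE form with no seriousness limit, and its item (iv) calls an open-ended class of drug reactions expected

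*Protocol*

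**What the plan says.** Section 9.3 sets the general rule: "Investigators will report all AEs that meet the definition of serious to the PC-CRTU", with a form for each event. Its subsection 9.3.1 then makes exceptions: "The following are regarded as expected events for the purpose of the trial and should not be reported on an SAE form". It adds: "These events should be collected on the routine CRFs instead".

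The four exempt items are:
- (i) "development of hyperkalaemia" (above 5.0 mmol/L)
- (ii) "a rise in creatinine to" above 220 µmol/L
- (iii) gynaecomastia
- (iv) "development of side effects requiring withdrawal of the trial treatment"

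Section 9.5.2 asks for SAE forms within 24 hours, but only for serious events that also require SAE reporting, so it carries the exception forward. Section 9.6 describes what the trials unit does on receipt of an SAE, including SUSAR classification. On oversight, section 9.9 says "The DMEC will review all SAEs".

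**The concern.** An exemption from the SAE form bites only on events that would otherwise go on one, because non-serious events never need it. Read literally, 9.3.1 therefore tells sites to withhold the form for a hospitalised or life-threatening case of a listed event. The listed events include toxicities that the protocol itself anticipates: section 8.3 expects potassium rises related to spironolactone in some patients.

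Item (iv) is of a different kind from the other three. It names no event. It defines the class by what happened to the drug, so the nature, severity and expectedness of the reaction play no part. At stake are the speed with which serious drug reactions are notified and whether an unexpected one is recognised as such through a defined procedure.

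**Working it through.** The protocol gives no figure to reproduce and no incidence from which to count affected events. The check is textual: follow each exempt item through the safety sections and look for any statement that brings serious cases back onto the SAE form.

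**1. Is there a seriousness limit?** Items (i) and (ii) have a lower threshold and no upper one. None of the four items excludes fatal, life-threatening, hospitalised, disabling or medically significant cases, which are the criteria in section 20. The general rule in 9.3 points the other way, but 9.3.1 sits beneath it as a stated exception and 9.5.2 is worded to respect that exception. No section restores the form for serious cases of items (i), (ii) or (iv).

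**2. What falls inside?** Compare the list with the reasons for stopping trial medication in section 8.4:
- Potassium above 5.5 mmol/L is inside item (i), since 5.5 exceeds 5.0. It is also the level that section 7.2 defines as drug toxicity.
- Creatinine above 220 µmol/L is item (ii).
- Gynaecomastia that persists after dose reduction is item (iii).
- Acute renal failure or creatinine clearance below 30 mL/min without the creatinine threshold, breast pain, and allergy are not named. They enter only through item (iv), because each is a reason to stop the drug.

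**3. What does the form trigger?** It triggers 24-hour notification (9.5.2), a reference number and SUSAR classification on receipt (9.6), and the DMEC's review of SAEs (9.9). The 7- and 15-day SUSAR reports in 9.7.1 and the annual report of SAEs and SARs in 9.7.2 need events to have been identified first. No expedited route is described that starts from a routine CRF.

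**4. How is expectedness judged?** Section 9.1 has the chief investigator assess the expectedness of all SARs, with reference to the SmPC. Section 9.5.2 uses the Reference Safety Information. Section 20 makes a reaction unexpected if its nature or severity is inconsistent with the product information. Section 9.3.1 item (iv) instead declares a reaction expected because treatment had to be withdrawn. The two tests cannot both govern the same reaction.

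**5. Can item (iv) capture a SUSAR?** Section 6.3 says that cases judged serious, unexpected and at least possibly related will be unblinded. The same section says that a patient whose code is broken is then withdrawn from trial treatment. Its examples of when unblinding may be essential are "acute liver injury, acute renal failure, Stevens-Johnson syndrome or agranulocytosis, if suspected to have been caused by spironolactone". A case that meets the SUSAR description therefore ends in withdrawal of treatment because of a suspected reaction, which can satisfy item (iv).

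**6. Do items (i) to (iii) raise the same SUSAR problem?** Only in part. An event listed as expected would ordinarily not be a SUSAR. Under section 20 it becomes one only if its severity goes beyond the product information.

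**The case against.** The best case for the protocol is that these events are not lost.
- Section 9.2 puts all AEs, including abnormal laboratory findings, on the CRF.
- Section 9.1 requires seriousness and causality to be assessed for every AE and expectedness for every SAR, and neither duty depends on an SAE form.
- Section 9.9 supplies data analyses to the DMEC and makes it responsible for regular monitoring of trial data. Its charter is not shown.
- Sections 9.7.1, 9.7.2 and 9.7.4 separately require SUSAR reports, annual reporting of SARs and immediate notice of significant safety issues.
- A general rule with a headed exception is a normal drafting form, so for items (i) to (iii) the relation between 9.3 and 9.3.1 need not be called a contradiction.

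All of this stands, and it rules out several stronger conclusions that a reader might draw:
- *That the DMEC would not see these events.* Nothing confines it to SAE forms.
- *That a reaction leading to withdrawal could never be classed as a SUSAR.* Under 6.3 the judgement of serious, unexpected and related comes before the unblinding and the withdrawal, and 9.1 allows that judgement without a form.
- *That SAE counts by arm would be biased towards spironolactone.* The exemption is applied blind and alike in both arms, SAE count is not a listed outcome, hospitalisations and major adverse clinical events are collected, and no event rates are given.
- *That all serious reactions leading to withdrawal are missed.* As a percentage this only restates item (iv).

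The objection does not supply an expedited route for serious listed events, and it does not reconcile item (iv) with the product-information test.

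A further objection is that limiting 9.3.1 to events meeting no seriousness criterion would leave it empty. It would still tell sites that crossing a laboratory threshold, or developing gynaecomastia, is not in itself a reason for an SAE form. That is useful because section 20 leaves medical significance to judgement.

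**Conclusion.** The point holds as a defect in the reporting route. A site that follows 9.3.1 as written would leave serious cases of the listed events off the SAE form, and so outside 24-hour reporting, SUSAR classification on receipt and the DMEC's SAE review. Item (iv) is the clearest error, since it is unbounded and conflicts with how 9.1, 9.5.2 and section 20 define expectedness. For items (i) to (iii) the loss is chiefly one of expedited reporting, and the SUSAR concern is confined to severity beyond the product information.

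The size is one of scope: all four items lack a seriousness limit and one has no bound on the type of event. How many events would be affected cannot be calculated. The conclusion assumes that sites apply 9.3.1 literally and that no procedure outside the protocol brings serious cases back. It does not extend to claims that the DMEC is blind to these harms, that SUSARs are impossible, or that the comparison between arms is biased.

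**What to change.** - Delete item (iv) of section 9.3.1.
- State that items (i) to (iii) are exempt only when no seriousness criterion in section 20 is met. A laboratory threshold or gynaecomastia alone would then not trigger an SAE form, but any case that is fatal, life-threatening, hospitalised, disabling or otherwise medically significant would.
- State that expectedness is judged against the Reference Safety Information in every case.
- Reconcile the wording of 9.3, 9.3.1, 9.5.2, 9.6 and 9.7 accordingly.

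The cost is a protocol amendment and a few more SAE forms. The change concerns reporting only and leaves dosing and the rules for stopping treatment untouched.
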